# Counteracting Age-related Loss of Skeletal Muscle Mass: a clinical and ethnological trial on the role of protein supplementation and training load (CALM Intervention Study): study protocol for a randomized controlled trial

**DOI:** 10.1186/s13063-016-1512-0

**Published:** 2016-08-09

**Keywords:** Elderly, Protein, Whey, Muscle, Strength training, Gut microbiome, Plasma metabolome

## Abstract

**Background:**

Aging is associated with decreased muscle mass and functional capacity, which in turn decrease quality of life. The number of citizens over the age of 65 years in the Western world will increase by 50 % over the next four decades, and this demographic shift brings forth new challenges at both societal and individual levels. Only a few longitudinal studies have been reported, but whey protein supplementation seems to improve muscle mass and function, and its combination with heavy strength training appears even more effective. However, heavy resistance training may reduce adherence to training, thereby attenuating the overall benefits of training. We hypothesize that light load resistance training is more efficient when both adherence and physical improvement are considered longitudinally. We launched the interdisciplinary project on Counteracting Age-related Loss of Skeletal Muscle Mass (CALM) to investigate the impact of lifestyle changes on physical and functional outcomes as well as everyday practices and habits in a qualitative context.

**Methods:**

We will randomize 205 participants older than 65 years to be given 1 year of two daily nutrient supplements with 10 g of sucrose and 20 g of either collagen protein, carbohydrates, or whey. Further, two groups will perform either heavy progressive resistance training or light load training on top of the whey supplement.

**Discussion:**

The primary outcome of the CALM Intervention Study is the change in thigh cross-sectional area. Moreover, we will evaluate changes in physical performance, muscle fiber type and acute anabolic response to whey protein ingestion, sensory adaptation, gut microbiome, and a range of other measures, combined with questionnaires on life quality and qualitative interviews with selected subjects. The CALM Intervention Study will generate scientific evidence and recommendations to counteract age-related loss of skeletal muscle mass in elderly individuals.

**Trial registration:**

ClinicalTrials.gov NCT02034760. Registered on 10 January 2014.

ClinicalTrials.gov NCT02115698. Registered on 14 April 2014.

Danish regional committee of the Capital Region H-4-2013-070. Registered on 4 July 2013.

Danish Data Protection Agency 2012-58-0004 – BBH-2015-001 I-Suite 03432. Registered on 9 January 2015.

## Background

On the basis of demographic extrapolations, the number of elderly citizens above the age of 65 years will increase in the next three decades by 50–200 %, with the specific proportion being dependent on country [1, 2]. With biological aging, physical function often decreases. This increases the risk of developing frailty [3], indicating higher risk for adverse events. Even in healthy, active, and independently living older people, a gradual loss of muscle mass, termed *sarcopenia* [4], takes place at an annual rate of up to 1–2 % starting in the sixth decade of life [5–7]. The loss of muscle mass is accompanied by an even faster deterioration of muscle strength of up to 3.5 % per year [8]. If allowed to progress, the development of sarcopenia is associated with increased risk of falling [9], decreased satisfaction with life [10], and even an increased mortality rate [11]. The impact of sarcopenic progression may become detrimental to an individual’s personal life and autonomy, and the societal implications are vast when one considers future healthcare and nursing expenditures. Therefore, in the present study, we aim to test the efficacy and feasibility of different strategies for counteracting muscular deterioration. Preferably, these strategies should be easy to integrate into everyday life for the majority of the aging population to induce maximal efficiency at both individual and societal levels.

Previous research has described the multifactorial nature of the development of sarcopenia [12–14]. On the basis of the aging muscle becoming less sensitive to daily anabolic stimuli due to protein intake [15] and muscular activity [16, 17], it is suggested that exactly these two factors possess a high potential to antagonize sarcopenia. Further, the nutrition and exercise training strategies are self-manageable, allowing a certain degree of flexibility for adjustment to personal preferences and everyday practices. Although their mutual dependency is acknowledged [18, 19], the “dosing” of each factor remains questionable, and the impact during long-term exposure is unknown. In contrast to studies of strategies used for treating individuals who already have loss of muscle mass and function, the aim of the Counteracting Age-related Loss of Skeletal Muscle Mass (CALM) Intervention Study is to evaluate strategies to prevent sarcopenic progression in healthy, independently living aging individuals.


Heavy load muscle training is undoubtedly the most effective exercise strategy to gain muscle mass and strength [45–48], and even very old individuals can benefit from training by experiencing an increase in muscle mass and strength [18, 19, 49–52]. However, at a societal level, the overall impact of implementing a certain training regime reflects a balance between the stimulatory effect of exercise training per se and tolerability and adherence to the training modality and setting. Activities of more moderate intensity, preferably those that are simple, convenient, and cheap [53], are associated with increased participation among the elderly. Further, these activities should be performed in an informal setting [54], and sessions in a training program seeking high adherence should be either home-based or conducted in smaller groups with peers [55, 56]. Therefore, despite an increased training effect per se, the feasibility of heavy load strength training requiring admittance to a fitness center or similar facility may be questionable for the elderly population [57]. As demonstrated in Fig. 1, home-based light load resistance training may prove to be a better recommendation for preventing age-related decreases in muscle mass and physical function because of increased adherence, but longitudinal research in the elderly is lacking.

**Fig. 1 Fig1:**
[figure not shown]
Hypothesized improvements over time with different interventions. *Black lines* mark the expected effect of per-protocol analysis: HRTW (*solid line*), LITW (*long*-*dashed line*), WHEY (*short-dashed line*), COLL (*dashed-dotted line*), and CARB (*dotted line*) interventions when analyzed per protocol. The *gray line* marks the expected effect intention-to-treat analysis of HRTW. *CARB* carbohydrate supplementation group, *COLL* collagen supplementation group, *HRTW* heavy resistance training with whey supplementation, *LITW* light-intensity training with whey supplementation, *WHEY* whey supplementation

We have launched a 1-year longitudinal randomized controlled trial (RCT), partly single-blinded/partly double-blinded, to investigate the impact of protein quality and training intensity on different variables. The primary outcome measure is the change in knee extensor skeletal muscle cross-sectional area (CSA) over the course of 1 year of intervention. The secondary and tertiary outcomes are listed in the Measurements section below. In this RCT, we are integrating the evaluation of the interventions’ impact on general health, physical and functional parameters, and impact on daily life routines and practices as well as on the acceptability of the interventions, covering the entire spectrum from objective physiological measures to subjective investigations on the participants. All results will be fed into the integrative and interdisciplinary outcomes of the CALM Intervention Study (Fig. 2).

**Fig. 2 Fig2:**
[figure not shown]
Spectrum of outcome variables. In the interdisciplinary Counteracting Age-related Loss of Skeletal Muscle Mass Intervention Study, we are investigating the entire spectrum of possible impacts of the intervention by applying objective, quantitative measures of the body and subjective, qualitative investigations of the participants

### Working hypotheses

We designed the CALM Intervention Study to investigate two overarching working hypotheses:

1. Whey protein hydrolysate supplementation is more efficient than collagen protein hydrolysate and carbohydrate in improving muscle size when administered to healthy elderly individuals.

2. With whey protein hydrolysate supplementation, the addition of center-based heavy resistance training is advantageous to home-based light load resistance training, and both of these regimens are superior to no training at all, in regard to improving muscle mass, overall health, and physiological parameters only with a per-protocol analysis. This will not be the case in regard to intention-to-treat analysis, where a markedly higher adherence is presumed in the home-based training group, leading to a similar or superior response compared to the center-based heavy resistance training group.

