### Statistics and power calculations

For all power calculations, we will apply a level of significance of 0.05 and a power of 0.80, and the primary outcome is the degree of muscle hypertrophy determined as the change in quadriceps muscle CSA on MRI scans over the course of the 12-month intervention. On the basis of previous data [91], we set the following parameters: least average expected change over the course of the 12-month intervention between distinct intervention groups, 300 mm^2^ (corresponding to an estimated relative change of 6.5 %) with a SD set to 140 mm^2^. Our goal is to be able to detect differences between groups’ mean hypertrophy down to approximately 2 %, which corresponds to approximately 80 mm^2^. A difference in the change of quadriceps muscle CSA greater than 80 mm^2^ between any two groups is statistically detectable with a power of at least 0.80 with a group size of 30. We decided to include 35 subjects in each of the three groups (HRTW, LITW, and CARB), as we anticipated a dropout rate of 15 % at the time of study initiation. In the WHEY and COLL groups, we expected a larger dropout rate because of taste issues with protein supplements and no motivational effect by training as in the HRTW and LITW groups. Thus, we will include 50 each in the WHEY and COLL groups. On an ad hoc basis, we will evaluate the actual dropout rate and adjust the total number of inclusions accordingly.

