In a subset of participants from the five intervention groups, we will conduct experimental tracer studies before and after the 12-month intervention period to determine the extent to which the interventions affect the responsiveness of MPS to protein intake. The goal is to measure whether any of the interventions enhance the anabolic sensitivity to protein intake and thereby investigate if we can link the observed differences in muscle mass over the course of the intervention period to changes in the anabolic response to protein feeding. Thus, the outcome measure is the relative change in the FSR of muscle proteins from the basal condition, defined as the overnight fasted and resting state, to the average 4-h postprandial period after intake of a standard protein bolus. We are not aware of any data on changes in MPS responsiveness over time, and we therefore based the power calculations on a sum of our own published and unpublished data obtained in healthy elderly participants. We established the following parameters: expected average 4-h postprandial responsiveness to protein feeding from basal condition of 0.016 %/h (i.e., approximately corresponding to an increase in muscle protein FSR of 50 %) with an interparticipant SD on the increase of 0.017 %/h. We aim to be able to detect a 50 % change in responsiveness within a group over the course of the 12-month period (i.e., a change of 0.008 %/h in the increase in the muscle protein FSR from 0.016 %/h to 0.024 %/h). The SD for the change in responsiveness is set as 0.006 %/h. By including 10–12 participants, we obtain a power of at least 0.80 to detect a statistical difference over time within each intervention group. By taking the probability of dropouts into account, we decided to include 12 participants in the HRTW, LITW, and CARB groups and 15 in the WHEY and COLL groups, respectively.

Investigators will analyze data as intention-to-treat (except in subgroup analyses) as well as per protocol, and we will test the following groups against each other using one-way analysis of variance of the relative group changes from baseline to 12 months: (1) WHEY vs. COLL vs. CARB and (2) HRTW vs. LITW vs. WHEY. We will not conduct any interim analyses in this project.

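### Hypothesis 2 predicts heavy training wins per protocol but not by intention to treat; the plan tests each set separately, so the second half can rest on a non-significant result

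*Protocol article*

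**What the plan says.** Under Working hypotheses, the protocol article expects HRTW to outdo LITW, and both to outdo no training, "only with a per-protocol analysis. This will not be the case in regard to intention-to-treat analysis". The stated reason is that "a markedly higher adherence is presumed in the home-based training group". The predicted result is that LITW does at least as well as HRTW, either equalling or beating it. No margin is given for similar.

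Under Statistics and power calculations, both an intention-to-treat and a per-protocol analysis are planned, subgroup analyses being exempt from the former. The test itself is fixed as follows: "we will test the following groups against each other using one-way analysis of variance of the relative group changes from baseline to 12 months". The training comparison is "2) HRTW vs. LITW vs. WHEY". For the power calculations, "we will apply a level of significance of 0.05 and a power of 0.80". The same section sets an SD of 140 mm² for the change in quadriceps cross-sectional area (CSA). It states that differences above 80 mm² between any two groups are detectable with power of at least 0.80 at 30 per group.

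**The concern.** The hypothesis has two limbs and a link between them. Per protocol, HRTW is better. By intention to treat, it is not. The link is that differing adherence accounts for the change. The planned ANOVA addresses the first limb. For the second it can give direct support only if LITW comes out significantly better. If the truth is that the arms are similar, the only support available is a test that fails to reach 0.05, and nothing planned estimates the link.

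A non-significant result in a trial of this size is compatible with a worthwhile advantage for HRTW. One significant and one non-significant test, in sets where one is nested in the other, is not a test of the difference between them. At stake is the trial's distinctive message: that home-based light training does as well as heavy training once adherence is counted.

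**Working it through.** **Inputs from the Statistics section.** SD 140 mm², target difference 80 mm², 30 evaluable per group, alpha 0.05 (taken as two-sided; the article does not say). The ANOVA is on relative change, but the SD is given only in mm², so the check is in mm².

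**The plan's own power figure.**
- Standard error of a difference = 140 × √(2/30) = 36.15 mm².
- Power at 80 mm² = Φ(80/36.15 − 1.96) = Φ(0.25) = 0.60, or 0.59 with the t distribution.
- The stated 0.80 is not reproduced; 49 per group would be needed. One-sided testing gives 0.72. So does a two-sided test at 92 mm², which is 2% on the scale where 300 mm² is 6.5%.

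A true intention-to-treat advantage of 80 mm² for HRTW is therefore missed about 40% of the time (1 − 0.60), or 28% on either kinder reading.

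**What an interval can show.** The 95% half-width at 30 per group is 2.00 × 36.15 = 72 mm². For the upper limit to fall below 80 mm², the observed HRTW minus LITW difference must be below about 80 − 72 = 8 mm². If the true difference is zero, the chance of this is Φ(80/36.15 − 1.96), again about 0.60; 80% power would need 49 per group. If HRTW is truly better by 80 mm², the rule wrongly passes in about 2.5% of trials.

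**Simulations** (30 per arm, SD 140 mm², two-sided t-tests; shift interval from a bootstrap within arm). Adherence rates and gains are assumptions, because the article gives none. LITW adherence is 90% throughout, and non-adherers gain nothing in cases A and B. The pattern means HRTW significantly better per protocol and the intention-to-treat test not significant.

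*A. Adherence matters.* Adherers gain 160 mm² (HRTW) or 80 mm² (LITW). The per-protocol difference is 80 mm². The intention-to-treat difference is 160 × HRTW adherence − 72.

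| HRTW adherence | True ITT difference | Pattern appears | Shift interval above zero |
|---|---|---|---|
| 50% | 8 mm² | 36% | 74% |
| 60% | 24 mm² | 34% | 62% |
| 70% | 40 mm² | 30% | 46% |

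*B. HRTW keeps a true 80 mm² intention-to-treat advantage, so the hypothesis is false.* LITW averages 0.9 × 80 = 72 mm² and HRTW 152 mm², so HRTW adherers gain 152/0.6 = 253 or 152/0.7 = 217 mm². The pattern appears in 42% to 52% of trials. The shift interval lies above zero in 70% to 91%.

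*C. Training has no effect, but adherers in both arms do better by 80 mm² for prognostic reasons.* Selection alone produces a shift of (0.9 − HRTW adherence) × 80 = 32, 24 or 16 mm² at 50%, 60% or 70%. The shift interval lies above zero in 15% to 23% of trials.

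*D. Adherence unrelated to outcome, true difference 0 to 80 mm².* The pattern appears in 1% to 5% of trials.

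**The case against.** The article states no decision rule. It calls these working hypotheses and does not say that Hypothesis 2 will be accepted from a pair of p-values. A separate analysis plan could add contrasts, a margin and a shift estimate, and their absence from an article is not in itself a fault. That stands as a limit. The point rests on what the article does fix: a hypothesis contrasting two sets, and a test that cannot establish the similar branch. It is also fair that a significant LITW advantage by intention to treat would support the superior branch directly.

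Three stronger readings are tempting and are not supported:

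- **That the hypothesis can be judged only by the significant/non-significant pattern.** The superior branch rules this out.
- **That the pattern usually fails to appear when the hypothesis is true.** In case A only the 50% row clearly fits the hypothesis. At 60% and 70%, HRTW is still truly better by 24 and 40 mm², and without a margin nobody can say whether that counts as similar.
- **That a shift interval excluding zero would settle the matter.** Case B shows such intervals in most trials where HRTW keeps a full 80 mm² advantage, and case C shows them arising from selection alone. A positive shift says the HRTW advantage is larger per protocol. It does not say the advantage is absent by intention to treat.

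Nor is the problem frequent false claims when adherence is irrelevant; case D shows those are uncommon.

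**Conclusion.** The concern holds in a limited form. For the similar branch of the intention-to-treat limb, the analysis fixed in the article offers only non-significance as evidence, and the change between analysis sets is not estimated. On the plan's own SD and group size, a real 80 mm² intention-to-treat advantage for HRTW goes undetected about 40% of the time. Under the assumptions of case B, the pattern that would be read as confirming the hypothesis appears in 42% to 52% of trials although the hypothesis is false.

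The 40% figure depends only on the plan's inputs and a two-sided test. The simulated figures depend on assumed adherence and gains and should be read as illustrations. The shortfall in the stated power is a separate matter that makes this one worse.

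**What to change.** In Statistics and power calculations, for Hypothesis 2:

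1. Report the HRTW minus LITW difference in 12-month quadriceps CSA change with a 95% interval, by intention to treat and per protocol.
2. State a margin in advance, for example the plan's own 80 mm². Claim similar or superior by intention to treat only if the upper limit of that interval lies below the margin, and never from non-significance.
3. Add the per-protocol minus intention-to-treat shift in this difference, with a 95% interval from a bootstrap that resamples participants within arm and recomputes both estimates each time. Make an interval above zero a required but not sufficient condition for an only-per-protocol claim. State that the shift also reflects selection into the per-protocol set, which randomisation does not protect.

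The cost is a few lines of analysis on data already being collected, since adherence is recorded in diaries and by trainers. The real price is candour. With a half-width of about 72 mm² at 30 per group, and roughly a 60% chance of meeting an 80 mm² margin even if the arms are truly equal, the trial will often have to report similarity as unproven.

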## Methods/design

### Overview

The CALM Intervention Study is a single-center, partly single- and partly double-blinded, multidisciplinary RCT. Collaborators are affiliated with (1) the Faculty of Science, Department of Food Science, (2) the Faculty of Humanities, SAXO Institute, and (3) the Faculty of Health and Medical Sciences, Department of Biomedical Sciences, all at the University of Copenhagen and the Institute of Sports Medicine Copenhagen, Bispebjerg Hospital, Copenhagen, Denmark. We wrote the protocol using the Standard Protocol Items: Recommendations for Interventional Trials (SPIRIT) guidelines for clinical trial protocols (http://www.spirit-statement.org/spirit-statement) and registered the protocol at ClinicalTrials.gov. Any changes will be reported there and to the local ethics committee.

### Recruitment of participants

The CALM Intervention Study will include 205 participants living in the Greater Copenhagen area through local newspapers, magazines, radio programs, social media, and presentations at senior centers and public events. See the Statistics and power calculations section below for further explanation on recruitment requirements. Recruitment commenced in January 2014. Exclusion criteria are listed in Table 1.

**Table 1 Tab1:** Exclusion criteria

	Criteria
1	Care dependency
2	Disability in lower extremities
3	Arthritis or arthrosis in knee or hip joints, arthritis requiring medication, or other rheumatic diseases potentially affecting joints or muscles
4	Diagnosed or suspected knee osteoarthritis (based on EULAR criteria: three symptoms and three signs); excluded if more than one of the following thee symptoms are found: morning stiffness <30 minutes, persistent knee pain, or functional limitations
5	Bilateral knee alloplastic and hip alloplastic material
6	Connective tissue disorders
7	Severe COPD (FEV_1_/FVC ratio <70 % and FEV_1_ < 50 % of predicted value (GOLD stage 3 or 4)
8	Unstable cardiac arrhythmias or decreased LVEF (<60 %)
9	Gut diseases affecting food absorption
10	Surgical diseases affecting ability to conduct heavy load strength exercise
11	Embodied magnetic metal
12	Endocrinological diseases potentially affecting muscles (diabetes mellitus, growth hormone-treated, sex hormone-treated, or untreated thyroid diseases)
13	Alcohol consumption >21 U/week for men and 14 U/week for women (1 U = 15.2 ml of alcohol)
14	Participation in studies using the same stable isotopically labeled tracers as this study (i.e., L-[ring-^13^C_6_]phenylalanine) within the last 6 months
15	Medications: systemic corticosteroids, sex hormone therapy, anti-sex hormone therapy, anticoagulants (thrombin inhibitors, K-vitamin antagonists, heparins, pentasaccharides, factor Xa inhibitors, thrombocyte inhibitors except nonsteroidal anti-inflammatory drugs and acetylsalicylic acid).
16	>1 h of weekly heavy strength training
17	Dementia or other severe cognitive impairment
18	Not holding Danish citizenship or not fluent in Danish

*Abbreviations: COPD* chronic obstructive pulmonary disease, *EULAR* European League Against Rheumatism, *FEV*
_*1*_ forced expiratory volume in 1 second, *FVC* forced vital capacity, *GOLD* Global Initiative for Chronic Obstructive Lung Disease, *LVEF* left ventricular ejection fraction

